## Abstract

**Background:**

Lifestyle and behaviour change are important factors in the prevention of cardiovascular disease and reduction of premature mortality. Public health initiatives have focused on opportunities for healthcare staff to deliver lifestyle advice routinely in primary and secondary care but there is no consistent approach to onward referrals and the rate of uptake of advice remains low. We do not know if advice is more effective in supporting behaviour change when a systematic approach is taken that includes identification of barriers to change, directing patients toward services, referral to services, and feedback on outcome.

**Methods and design:**

This is a single-centre, randomized, unblinded feasibility trial in an acute hospital setting which aims to assess the feasibility of a definitive trial and provide proof of concept for the systematic delivery of individualized lifestyle advice in patients managed through an acute cardiology in-patient service.

Patients will be recruited before discharge and randomized to two groups. A control group will receive the usual lifestyle assessment and referral, while an intervention group will receive the usual assessment plus the new individualized lifestyle assessment and referral. The new assessment will inform assignment of each patient to one of three categories based on personal barriers to change. Patients may be referred to a formal lifestyle-change programme, through the ‘Leeds Let’s Change’ website, or they may be guided in self-management, using goal setting, or they may be assigned to a ‘deferment’ category, for reassessment at follow-up. These latter patients will be given a contact card for the ‘Leeds Let’s Change’ service.

**Discussion:**

Lifestyle change is an important mechanism for improving health and wellbeing across the population but there are widely acknowledged difficulties in addressing lifestyle factors with patients and supporting behaviour change. A systematic approach to assessment would facilitate audit and provide an indicator of the quality of care. The new assessment template has been designed to be quick and easy to use in practice and could, for example, be added to a primary care consultation or form part of a nursing discharge assessment in an acute setting.

**Trial registration:**

Current Controlled Trials ISRCTN41781196.

## Background

Cardiovascular disease is a global killer; it is a major cause of premature death and morbidity, and is responsible for over 4 million deaths in Europe annually [1]. It is clear that promoting good cardiovascular health has numerous benefits for society, including lower levels of morbidity, better wellbeing (or quality of life) and lower healthcare costs. Nevertheless, tackling the lifestyle behaviours associated with cardiovascular risk with interventions like smoking cessation, weight management, alcohol awareness and exercise is complex, as many factors, be they social and psychological, cultural or economic, may affect the individual’s willingness and ability to change [2-4].

Recent guidance from the UK’s National Institute for Health and Clinical Excellence (NICE) [5] states that attempts to change behaviour have been largely unsuccessful and that there is ‘…no strategic approach to behaviour change across government, the NHS or other sectors, and many different models, methods and theories are being used in an uncoordinated way.’ This, NICE concludes, is despite a mass of evidence from different disciplines on the theoretical basis for individual and societal-level behaviours and models of change. Divergent conceptual approaches and heterogeneous research methods make it difficult to merge evidence to inform the planning and design of services and their delivery.

Public health initiatives have focused on the opportunities to deliver lifestyle advice [3]. Healthcare staff in primary and secondary care routinely discuss lifestyle with patients but there is no consistent approach to the referral of patients to receive the support or services required for change. Moreover, the rate of uptake of lifestyle support services remains low [6]. In our previous work [4,7], we identified five individual barriers to behaviour change:

• Low mood, especially anxiety and depression.

• Poor knowledge about healthy lifestyles and poor education.

• Little support from family and friends.

• Financial and transport difficulties (where cost and travel is required for attendance at a lifestyle programme).

• A belief that changing lifestyle will have little impact on health.

The intervention to be tested will therefore consist of a new referral assessment for patients. The assessment will address these barriers to change and will be used to identify suitable services for patients.

### Financial incentives

Incentivizing individuals to encourage healthy living was recently discussed by the National Institute for Health and Clinical Excellence (NICE) Citizen’s Council [8]. This approach is already being implemented, for example, the ‘Help 2 Quit’ programme run by Shropshire NHS [9]; the ‘Give It Up For Baby’ run by NHS Tayside [10] offering incentives to pregnant women who quit smoking, and an NHS PCT in the south of England [11] offering financial incentives for weight loss.

Incentives are becoming more common in public health interventions for encouraging healthy behaviour, and some positive results have been reported for increasing weight loss [12], and levels of physical activity [13]. Nevertheless, while the use of incentives in this way may be a useful tool in encouraging behaviour change, recent reviews suggest that further research is needed to justify their widespread use [14,15]. This study will add to knowledge about the nature and scale of incentives that people deem acceptable.

This randomized feasibility trial is being conducted as part of the vascular research theme: Improving Prevention of Vascular Events (IMPROVE) in the National Institute for Health Research Collaboration for Leadership in Applied Health Research and Care (CLAHRC) for Leeds, York and Bradford. It will examine feasibility and provide proof-of-concept evidence for a larger-scale trial to test the hypothesis that the rate of uptake of lifestyle behaviour change can be increased by use of a systematic assessment that tailors the level of lifestyle support offered to individuals according to personal barriers and facilitators to lifestyle behaviour change. It is exploratory in nature rather than a scaled-down, pilot version of the main trial. The design of the main trial may be modified based on the findings of the feasibility trial.

The intervention (a lifestyle referral assessment) is based on evidence about key factors that are known to predict uptake of lifestyle behaviour change [2,4], and is specifically designed for use by care providers at the point where they might advise patients of lifestyle support services or refer patients to these support services. It incorporates a discussion of barriers and facilitators to changing lifestyle before offering an individualized plan or referral to an appropriate service through *Leeds Let’s Change*[16], a locally provided NHS website that provides information on services that support lifestyle change. The control action is the usual healthy-living assessment that has been implemented in local cardiology services, and which identifies behaviours and offers brief lifestyle advice (including a ‘Leeds Let’s Change’ card).

### Ethical approval

This study was approved by the committee of the National Research Ethics Service for Yorkshire and the Humber (Leeds East) on 12 March 2012. REC Reference number: 12/YH/0086.

### Aims and objectives

The main aim of the study is to assess the feasibility of conducting a definitive trial in terms of recruitment, use and acceptability of the intervention, follow-up at 3 and 6 months, and data collection methods. The following criteria will be used to assess success:

1. Favourable difference shown in referrals and participation.

2. Favourable changes made through self-management.

3. Recruitment target met in time available.

4. Retention rate at 75% or more at 6 months follow-up.

5. Missing data at 10% or less, including 6 months follow-up.

6. Included participants are representative of the target population.

In addition, the study aims to establish suitable procedures for delivering the intervention and conducting assessments and procedures for ensuring recruitment and retention in the study. Finally, the study aims to discover whether using a structured, individualized approach to lifestyle assessment and referral will improve uptake and participation in lifestyle- and behaviour-change interventions;

The study will also examine, qualitatively, the acceptability of the assessment tool to patients in an acute cardiology setting as well as patients’ experiences of making lifestyle changes in order to develop effective recruitment and retention strategies.

The study will have a number of quantitative objectives:

1. To determine how many patients accept referral to a formal lifestyle programme;

2. To determine how many patients participate in a lifestyle-change intervention or initiate self-managed change;

3. To investigate the uptake of lifestyle intervention in relation to subsequent behaviour change and impact on health-related quality of life, mood and social satisfaction;

4. To estimate feasible eligibility, recruitment and refusal rates, and 3- and 6-months follow-up rates;

5. To measure key outcome domains (that is, for completion rates, missing data, estimates, variances and 95% confidence intervals for the difference between the control and intervention groups) for patients including clinical indicators and patient-reported measures of social satisfaction; health-related quality of life; and mood;

6. To synthesize data to inform the sample size of a definitive trial;

7. To determine the acceptability (and factors influencing this) of financial incentives as a method to encourage behaviour change, their pricing and factors influencing this.

## Methods and design

This study is being conducted in cardiology wards at the Leeds Teaching Hospitals Trust with patients admitted to hospital, who are subsequently referred to the cardiac rehabilitation team or discharged with no confirmed diagnosis of cardiac event.

### Trial design

The study is designed as a single-centre, randomized, unblinded feasibility trial in an acute hospital setting (Figure 1).

**Figure 1 F1:**
[figure not shown]
Trial design summary.

### Incentives sub-study

A sub-study will explore the acceptability and potential usefulness of using financial incentives to help patients overcome motivational and financial barriers to changing their health behaviour. Incentives will not be offered within the trial but we will explore theoretical aspects, such as the pricing and type of incentives offered, and the association of type and magnitude of incentive with perceived difficulty of change. A survey questionnaire specifically designed to explore attitudes to incentives will form part of the study assessments.

### Study conditions

Participants are randomized, using block randomization with randomly varying block sizes, in equal proportions, with no stratification, to receive either usual lifestyle assessment or an enhanced lifestyle assessment using an automated 24-hour telephone randomization service provided by the clinical trials research unit. The usual lifestyle assessment comprises a series of questions that identify lifestyle factors (that is, smoking habits, alcohol consumption, physical activity and weight) that contribute to an increased risk of vascular events. The enhanced lifestyle assessment includes the usual assessment but also contains an evidence-based lifestyle referral assessment based on factors that predict change [2,4]. The aim of this enhanced assessment is to aid healthcare professionals in directing patients toward appropriate lifestyle-change interventions. The assessments are delivered in the hospital ward by research staff before discharge.

### Eligibility criteria

Men or women aged between 40 and 74 years of age at the time of screening, who are willing and able to give written informed consent, and have been admitted to hospital with a diagnosis of acute coronary event, myocardial infarction or symptoms of a cardiac nature will be eligible for inclusion in the study.

Patients who are currently receiving specialist treatment with a primary focus on alcohol, smoking, diet or exercise, or who have no modifiable risk factors for vascular events will be excluded from the study. In addition, patients who will be unavailable for follow-up because they have no fixed abode, are mainly resident abroad, or are currently serving a sentence in prison or have outstanding legal issues likely to lead to imprisonment will be excluded, as will patients who are unable to take part in either intervention using spoken English or are unable to complete the English-language outcome measure tools without assistance.

### Potential sample

Based on figures available at the planning stage, we can estimate that cardiology services in the Leeds Teaching Hospitals Trust receive around 800 admissions per month; on average approximately 300 of these admissions are people who have had an acute myocardial infarction and 150 are people who have experienced an acute cardiac event; the remainder are elective admissions for cardiac-related procedures such as stenting. It is therefore estimated that ten patients per week could take part in the study. This estimate is also based on local knowledge and previous experience of recruiting patients with acute stroke in a similar setting [17].

### Recruitment strategy

All patients admitted to the selected wards are considered potential participants. Potentially eligible patients are identified by research staff from the ward admissions register or by direct referral from ward staff. These patients are approached by the research team or ward staff to determine willingness to participate and an eligibility checklist is completed. Assessment of psychological status and cognitive capacity to participate is made in consultation with ward staff. All patients meeting the eligibility criteria are provided with an explanation of the study and a patient information sheet, and have an opportunity to ask questions. If willing to continue, they are invited to participate in the study and give written consent. Participation in the study does not alter their usual care. Reasons for nonparticipation, date of birth, sex and postcode are recorded whenever possible.

### Recruitment rates, exclusions and generalizability

The rates of recruitment to the trial are given in Figure 2. Figure 3 provides the numbers of participants at each stage in the trial. Details of the patients are summarized in Table 1.

**Figure 2 F2:**
[figure not shown]
**Recruitment: predicted, weekly and cumulative accrual rates.** Cum, cumulative; Exp, expected.

**Figure 3 F3:**
[figure not shown]
Passage of participants through trial.

**Table 1 T1:** Patient characteristics in the screened and randomized samples

	**Screened (*****n *****= 887)**	**Randomized (*****n *****= 132)**
Age (years)		
Up to 35	32 (3.6)	0 (0.0)
35 to 40	13 (1.5)	0 (0.0)
40 to 50	82 (9.3)	25 (18.9)
50 to 60	149 (16.9)	44 (33.3)
60 to 70	163 (18.5)	44 (33.3)
70 to 75	107 (12.1)	19 (14.4)
75 to 80	130 (14.7)	0 (0.0)
80 to 85	122 (13.8)	0 (0.0)
85 and over	85 (9.6)	0 (0.0)
Male	467 (52.6)	81 (61.4)
Female	420 (47.4)	51 (38.6)

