**Reasons for admission**		
Symptoms	718 (81.0)	116 (87.9)
Acute coronary event	97 (10.9)	15 (11.4)
Elective procedure	26 (2.9)	0 (0.0)
Atrial fibrillation	10 (1.1)	1 (0.8)
Other	6 (0.7)	0 (0.0)
Unknown	30 (3.4)	0 (0.0)

Data are *n* (%). Age is available for 883 screened patients.

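### Table 1, the only comparison offered on generalizability, uses all screened patients, 43% of them outside the age limits, and is a poor basis for success criterion 6

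*Protocol article*

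**What the plan says.** Under Aims and objectives, success criterion 6 reads "Included participants are representative of the target population". No comparator or threshold is attached to it. The Discussion makes development of the large-scale trial depend on the success criteria being met, so the criterion bears on the progression decision.

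Eligibility criteria admits "Men or women aged between 40 and 74 years of age at the time of screening". Recruitment strategy treats everyone admitted to the selected wards as a potential participant, so the screening log also holds people who could not enter.

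The section headed "Recruitment rates, exclusions and generalizability" refers to Table 1 for patient details. That table, "Patient characteristics in the screened and randomized samples", has two columns: screened (n = 887) and randomized (n = 132). Its footnote says "Age is available for 883 screened patients". There is no column for eligible, age-eligible or eligible but not randomized patients.

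The data for a better comparator are collected at least in part: "Reasons for nonparticipation, date of birth, sex and postcode are recorded whenever possible".

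**The concern.** Two processes separate the screened from the randomized. One is exclusion by rule, which is known in advance and defines the population the trial means to study. The other is selection among those who meet the rules: who is approached, who agrees, who is missed. Representativeness of the target population concerns the second. A comparison with all screened patients adds the two together.

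Because a large share of the screened lie outside the age limits, every eligible band is a smaller percentage of the screened column than of the eligible population. Under-recruitment of an eligible band can then look like adequate or even generous recruitment. If criterion 6 were judged from Table 1 as printed, the judgement on the oldest eligible patients could come out in the wrong direction.

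**Working it through.** **Inputs.** All counts are from Table 1; the age limits are from Eligibility criteria. Bands are read as including the lower limit and excluding the upper, so 40 to 75 in the table matches ages 40 to 74.

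**Reproducing the printed figures.** The nine screened age counts sum to 883 and the randomized counts to 132. For ages 70 to 75, 107/883 = 12.1% and 19/132 = 14.4%, as printed. The other age percentages also reproduce.

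**Share outside the age limits.** 32 + 13 + 130 + 122 + 85 = 382, and 382/883 = 43.3%. Of these, 45 are under 40 and 337 are 75 or over.

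**Restricting to the eligible ages.** 82 + 149 + 163 + 107 = 501. The non-randomized are the screened minus the randomized in each band (57, 105, 119 and 88; total 369).

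| Age band | All screened (n = 883) | Age-eligible screened (n = 501) | Age-eligible, not randomized (n = 369) | Randomized (n = 132) | Randomized / age-eligible |
|---|---|---|---|---|---|
| 40 to 50 | 9.3% | 16.4% | 15.4% | 18.9% | 25/82 = 30.5% |
| 50 to 60 | 16.9% | 29.7% | 28.5% | 33.3% | 44/149 = 29.5% |
| 60 to 70 | 18.5% | 32.5% | 32.2% | 33.3% | 44/163 = 27.0% |
| 70 to 75 | 12.1% | 21.4% | 23.8% | 14.4% | 19/107 = 17.8% |

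For ages 70 to 75, the randomized share divided by the screened share is 14.4/12.1 = 1.19 as printed, and (19/132)/(107/501) = 0.67 after restriction.

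**Missing ages.** Four screened patients have no recorded age. If all four were age-eligible, the 70 to 75 share would lie between 107/505 = 21.2% and 111/505 = 22.0%. The direction does not change.

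**Strength of evidence.** Randomized versus not, over four bands: Pearson chi-square 5.61 on 3 degrees of freedom, p = 0.13. Ages 70 to 75 against 40 to 70 (19/107 v 113/394 = 28.7%): odds ratio 0.54, Fisher p = 0.026. The second contrast was chosen after seeing the data and carries less weight than the first.

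**How much the other exclusions would have to explain.** 17.8/28.7 = 0.62. The shortfall would vanish if the proportion of 70 to 75 year olds meeting the remaining criteria were about 0.62 times that in the younger bands. The article gives no figure by which to judge this.

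**The case against.** The article nowhere says that Table 1 is the test of criterion 6. The link is inferred from the section heading and from the absence of any other comparison of characteristics. The full protocol or an analysis plan may define the comparison properly. This stands, and the point is limited accordingly: the comparison that is published should not be the one used.

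Table 1 also hides nothing. Its bands break at the age limits and the ineligible bands show no randomized patients, so a reader can restrict it unaided. The printed randomized-to-screened ratios across the four eligible bands are 18.9/9.3 = 2.03, 33.3/16.9 = 1.97, 33.3/18.5 = 1.80 and 14.4/12.1 = 1.19, which already rank the oldest band lowest. This too stands: the misleading impression arises when the 70 to 75 row is read alone. That is how such a table is commonly read, and an eligible column would prevent it.

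The 501 are eligible by age only. Current specialist treatment, absence of modifiable risk factors, unavailability for follow-up, language, and the ward judgement of psychological status and cognitive capacity may all vary with age. This stands and rules out a claim of proven under-recruitment.

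A reader might infer more from the same table; the article does not support it:

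- That the difference in sex (52.6% male among screened, 61.4% among randomized) is an artefact of age exclusion. Sex is not cross-tabulated with age, so this cannot be checked.
- That recruitment yield is understated. The article's text states no yield, and eligibility, recruitment and refusal rates are assigned to the flow diagram, which is not available here.
- That the case mix departs from plan, because Potential sample expects that "approximately 300 of these admissions are people who have had an acute myocardial infarction" while few of the randomized were admitted with an acute coronary event. The planning figures are for all cardiology services and count people with an event. Table 1 gives reason for admission on selected wards, where a symptom admission may later be confirmed as an event. The two are not like for like.

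**Conclusion.** The point holds in a limited form. The published comparison uses a reference group of whom 43.3% were barred by age, and it is a poor basis for criterion 6. For the oldest eligible band the row-level impression changes direction once the reference is restricted: from 14.4% v 12.1% to 14.4% v 21.4%.

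The counts are firm and do not depend on the four missing ages. What they mean is less firm. They suggest that patients aged 70 to 75 may have been under-recruited. It is tempting to call this demonstrated under-recruitment, but the fully eligible denominator is unknown and the overall test gives p = 0.13. The conclusion also assumes that the randomized are a subset of the screened, and that no better comparison sits in a document not shown.

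**What to change.** State that criterion 6 will be judged by comparing randomized patients with eligible patients who were not randomized. Where full eligibility was not established, use the age-eligible, non-elective screened patients as the minimum. Compare age, sex, reason for admission and, where recorded, postcode. Add that group as a column in Table 1 and keep the all-screened column for description.

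Report the differences descriptively, in line with the article's emphasis on estimation, and state how many non-participants lack each item.

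The cost is re-tabulation of screening data already held. The drawback is that details of non-participants are recorded only where possible, so the new column will be incomplete for some of them. A separate set of results for the 15 randomized patients with an acute coronary event is not recommended: split over two arms, it would tell little.
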